### Statistical analysis

Statistical analyses will include an intent to treat (ITT) analysis including all participants enrolled and a per protocol analysis using all participants who complete the study without major protocol violations. Descriptive analyses will be performed by cross-tabulating relevant predictors (e.g. demographic variables) and endpoints. Appropriate statistical tests will be carried out, such as Fisher’s exact test for categorical variables and Wilcoxon tests for continuous variables. Univariable regression analyses will also be performed to estimate regression coefficients and their 95% confidence intervals. Data analysis will occur when the study is complete. Interim analyses of safety data will be conducted at the end of FU1 and at the end of FU2. The comprehensive statistical analysis plan will be finalised prior to the final analysis.

All participants who receive at least one dose of IMP will be included in the safety analysis set. All participants who receive at least one dose of the IMP and undergo disease re-evaluation as per protocol will be included in the efficacy analysis. Due to the exploratory nature of the study with regards to efficacy endpoints, pathologic response rates and RECIST 1.1 response rates will be presented descriptively. The exploratory endpoint of PFS rate will be shown with Kaplan-Meier plots using the full timespan from the start of IMP administration until the date of progression or death from any cause. Proportions of participants who do not progress and who are alive at Day 127 (FU2) and 4-monthly time-points thereafter will also be estimated. For the exploratory endpoints, appropriate descriptive analysis and univariable regression analysis will be conducted.

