## Methods/design

PRIME HCC is a two-part, phase Ib study of ipilimumab and nivolumab combination prior to LR in adult patients (aged ≥18 years) with HCC. Ipilimumab will be administered once only on Day 1. Nivolumab will be administered on Day 1 and Day 22 (± 3 days) for a total of two 21-day cycles (i.e. 6 weeks of treatment). Part 1 of the study will initially consist of a safety run-in phase of 6 participants. If two or fewer surgical delays are observed, the study will continue to Part 2, which will consist of an expansion phase including up to 26 participants. All participants entered into the study will receive nivolumab and ipilimumab for a fixed duration of 6 weeks of treatment. The study flow-chart is summarized in Fig. 1**.**

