### Planned sample size and study period

We designed the study as a safety-oriented trial and considered enrolling a cohort of up to 32 participants to:
Comprehensively characterise the safety profile of nivolumab and ipilimumab co-administration in patients with early-stage HCC;Preliminarily document the efficacy of treatment to inform subsequent efficacy-testing in a future adequately powered trial;Obtain adequate information regarding the disease-modulating effects from treatment reflected by the proposed exploratory endpoints.

With the primary endpoint being safety, no power calculation for hypothesis testing is required to formally power the study: the upper 95% confidence interval for toxicity events will inform the decision to proceed to a future, adequately powered, phase II trial. Part 1 of the study will initially require a total of 6 patients. If ≤2 surgical. Delays are observed (primary safety endpoint), the study will continue to Part 2 following Independent Safety Data Monitoring Committee review of preliminary safety data. A second interim analysis will be performed when 100% of the recruited patients have completed study follow-up visit 2 (FU2) to evaluate general safety and tolerability of the combination.

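### The efficacy set drops dosed patients who are never re-evaluated, although PFS runs from first dose, so the descriptive ORR and PFS rates are likely to be overstated

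*Protocol article*

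**What the plan says.** The Statistical analysis section of the protocol article names four populations:

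- "an intent to treat (ITT) analysis including all participants enrolled";
- "a per protocol analysis using all participants who complete the study without major protocol violations";
- a safety set of everyone who received any study drug;
- an efficacy set, limited to those who "receive at least one dose of the IMP and undergo disease re-evaluation as per protocol will be included in the efficacy analysis".

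The same section draws the PFS curve "from the start of IMP administration until the date of progression or death from any cause". It also plans the proportions alive and progression-free at Day 127 and every four months after that.

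Under Outcome measures and endpoints, ORR is read on imaging before resection at Day 42, and pathologic response is read on the resected specimen. Both are secondary, and PFS is exploratory. Study procedures places the first repeat scan at Day 43, the next at Day 127, and follow-up at two years per patient.

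The article does not say how a dosed patient without re-evaluation is counted, or what completing the study means.

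**The concern.** Entry to the efficacy set depends on something that happens after treatment starts. A patient who receives study drug and then dies, deteriorates or drops out before any re-evaluation is not counted as a failure. That patient is not counted at all.

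For PFS, this conflicts with the section's own definition. The clock starts at first dose and death is an event, but nobody can enter the set without having reached a re-evaluation. On that set, the roughly six weeks before the first scheduled scan are guaranteed free of deaths. For ORR, the denominator shrinks while the number of responders stays the same.

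The rates have a use beyond this trial. Planned sample size and study period lists preliminary documentation of efficacy, to inform a later powered trial, among the reasons for the cohort. A planning rate that leaves out early failures would make that later trial too small.

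**Working it through.** **The plan's own figure.** The article states "considered enrolling a cohort of up to 32 participants". This is the sum of a "safety run-in phase of 6 participants" and "an expansion phase including up to 26 participants": 6 + 26 = 32, which reproduces. There is no power calculation to check, since the article says "no power calculation for hypothesis testing is required to formally power the study". It also states no expected response rate or PFS rate for this trial, and no expected number of non-evaluable patients.

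**Inputs.** N = 32 dosed, the stated maximum. The rest are assumptions:

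- k = 1, 2, 3 or 5 dosed patients without any re-evaluation.
- x = 10 responders, because the Background cites an ORR of 31% for the combination in advanced disease and 0.31 × 32 = 9.9. As a low case, x = 4, from the 14% cited for nivolumab alone (0.14 × 32 = 4.5, taken as 4).
- e = 4 PFS events between re-evaluation and Day 127, with e = 6 as a variant.

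**Formulas.** The k patients are counted as failures in the all-dosed rate and are absent from the efficacy set.

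- ORR: x/N on all dosed, x/(N − k) in the efficacy set.
- Day-127 PFS: (N − k − e)/N on all dosed, (N − k − e)/(N − k) in the efficacy set.

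**Results for x = 10 and e = 4.**

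| k | ORR, all dosed | ORR, efficacy set | Shift (points) | PFS, all dosed | PFS, efficacy set | Shift (points) |
|---|---|---|---|---|---|---|
| 1 | 10/32 = 31.3% | 10/31 = 32.3% | +1.0 | 27/32 = 84.4% | 27/31 = 87.1% | +2.7 |
| 2 | 31.3% | 10/30 = 33.3% | +2.1 | 26/32 = 81.3% | 26/30 = 86.7% | +5.4 |
| 3 | 31.3% | 10/29 = 34.5% | +3.2 | 25/32 = 78.1% | 25/29 = 86.2% | +8.1 |
| 5 | 31.3% | 10/27 = 37.0% | +5.8 | 23/32 = 71.9% | 23/27 = 85.2% | +13.3 |

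With x = 4, the ORR shift is 0.4 to 2.3 points. With e = 6, the PFS shift is 2.5 to 12.2 points. The Clopper-Pearson 95% interval for 10/32 is 16.1% to 50.0%, so every ORR shift lies well inside sampling error.

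The PFS columns take all k patients as deaths or progressions before re-evaluation. A patient who leaves event-free would be censored, so the PFS shift would then be smaller.

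**How many might be missing.** The nearest figures in the article are discontinuation rates for the combination in advanced disease: 2% in the Abstract and 5% in the Background. If each discontinuation meant no re-evaluation, which is an assumption, 0.02 × 32 = 0.6 or 0.05 × 32 = 1.6 patients would be lost. The chance of losing at least one is 1 − 0.98^32 = 48% or 1 − 0.95^32 = 81%. At an assumed 10% or 15%, the expected loss is 3.2 or 4.8 patients.

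**Direction.** Suppose 10 of the 32 would respond if all were assessed, and r of the k missing patients are among those 10. The efficacy-set ORR is then (10 − r)/(32 − k). This exceeds 10/32 only when r < 10k/32 = 0.3125k. If re-evaluation is missing independently of outcome, the expected bias is zero.

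**The case against.** The strongest reply is that this is a descriptive phase Ib trial with safety as its primary endpoint. The safety set already takes everyone dosed, and the decision to go on to phase II rests on the upper confidence limit for toxicity. Evaluable-patient sets are common in trials of this size. An ITT analysis of all enrolled is planned, and the full analysis plan, not shown here, may assign sets to endpoints. Stopping drug for toxicity does not stop imaging, and patients fit for resection should seldom die within six weeks. These points limit the severity. They do not remove the concern, because the article states a rule for who enters the efficacy analysis. ITT is named without being attached to ORR or PFS.

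Three stronger readings are tempting but not supported:

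- **That the rates are conditioned on survival generally.** They are not. Deaths after re-evaluation still count. The criterion also does not name the Day 43 scan, so a patient who misses that one but is scanned later may still enter.
- **That upward bias is certain or large.** No number of missing patients can be taken from the article. The cited discontinuation rates suggest about one or two, which is the low end of the table.
- **That per-protocol survival is 100% by construction.** With 6 deaths, for example, 26/32 = 81% would become 26/26. But this requires completing the study to mean being alive at two years, and the article never says so. A patient followed until death may count as having completed.

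**Conclusion.** The point holds in limited form. The efficacy set selects on a post-treatment event, and this conflicts with a PFS definition that starts at first dose and counts death. Upward bias in ORR and PFS is likely if re-evaluation is missed because of toxicity, progression or death, and absent if it is missed independently of outcome.

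The size is about 1 to 6 points for ORR (32 dosed, 10 responders) and about 3 to 13 points for Day-127 PFS (4 later events). This assumes 1 to 5 patients without re-evaluation, all of them failures. All counts except 32 are assumptions.

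Pathologic response has a related weakness: it can be read only in resected patients, and the article does not say how unresected patients are counted. The per-protocol wording is a risk rather than a shown bias, since an undefined notion of completion could let an outcome remove a patient.

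Severity is moderate. The affected endpoints are secondary or exploratory and descriptive, and the primary safety conclusion is untouched. They are nevertheless meant to inform a later trial.

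**What to change.** In the analysis plan, before the final analysis:

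1. Make all dosed participants the main set for ORR and PFS. Count a patient without re-evaluation as a non-responder, and a death before re-evaluation as a PFS event timed from first dose.
2. Report pathologic response on all dosed participants, with unresected patients counted as no response, alongside the rate in the resected subset.
3. Keep the re-evaluable set as supportive, and report how many dosed patients it leaves out and why.
4. Define the per-protocol set by eligibility and dosing violations, so that death or progression cannot remove a patient as a non-completer.

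The cost is a change of wording, with no new data and no change to sample size. Headline rates become slightly lower.

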### Study procedures

Patients will undergo baseline tumour imaging including computed tomography (CT) scan of the chest, abdomen and pelvis, and by contrast enhanced magnetic resonance imaging (MRI) scan of the liver at screening. At post-treatment time-points prior to surgery (on Day 43), after surgery (on Day 127) and 4-monthly thereafter, tumour imaging will be repeated using contrast enhanced MRI. A triple-phase CT of the liver is an acceptable alternative for intrahepatic staging in patients with contraindications to MRI. Baseline CT/MRI scans do not need to be repeated if obtained within 35 days of first dose. The same method used for assessment at baseline must then be used at all subsequent time points. RECIST v1.1 criteria will be used to determine patient response to treatment, progression-free survival (PFS) and ORR. A baseline core tumor biopsy will be collected from participants at screening and patients will have a parcel of leftover tissue from their LR specimen stored for correlative studies. Treatment will consist of a maximum of 2 cycles of nivolumab 3 mg/kg and 1 cycle of ipilimumab 1 mg/kg administered intravenously Q3W. Patients will be reviewed following completion of IMP treatment (Follow-up visit 1; FU1) on Day 43 +/− 3, prior to surgery. LR will be performed as per standard of care. The safety FU2 will be conducted 126 days (± 7 days) after the first dose of the investigational medicinal product (IMP). All AEs that occur prior to the visit will be recorded. Participants with on-going AEs at the visit will be followed up by principal investigator (PI) or delegate until resolution or stabilisation of the event. Following FU2, participants will be assessed every 4 months (± 7 days) thereafter to collect information regarding disease status and survival. Long-term follow-up will continue, for each patient, for a total of 2 years. The Standard Protocol Items: Recommendations for Interventional Trials (SPIRIT) schedule of enrolment, interventions, and assessments is provided in Supplementary Table 1**.**

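### The efficacy set requires a re-evaluation after dosing, so dosed participants lost before it leave the ORR denominator and deaths before it cannot count in PFS; the ITT set is not reconciled with this

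*Protocol article*

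**What the plan says.** The Statistical analysis section of the protocol article names several analysis sets.

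- **ITT and per protocol.** The section opens with "an intent to treat (ITT) analysis including all participants enrolled" and adds a per-protocol analysis. Neither is tied to a particular endpoint.
- **Safety set.** "All participants who receive at least one dose of IMP will be included in the safety analysis set". One dose is the only condition.
- **Efficacy set.** Those who "receive at least one dose of the IMP and undergo disease re-evaluation as per protocol will be included in the efficacy analysis". This adds a second condition, met only after dosing has begun.

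The text that follows the efficacy set describes pathologic and RECIST response rates, then Kaplan-Meier PFS "using the full timespan from the start of IMP administration until the date of progression or death from any cause", then the proportions alive and progression-free at Day 127 and every four months after that.

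Study procedures gives the imaging times: "At post-treatment time-points prior to surgery (on Day 43), after surgery (on Day 127) and 4-monthly thereafter". The first follow-up visit is set "on Day 43 +/− 3, prior to surgery". Outcome measures and endpoints takes ORR, a secondary endpoint, from the pre-resection scan. It labels that scan day 42 rather than Day 43, which does not affect this point. PFS and OS are exploratory.

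**The concern.** Whether a participant enters the efficacy set depends on reaching a scan about six weeks after treatment starts. Those who do not reach it are unlikely to be a random subset: they include anyone who died, deteriorated or withdrew first. This has two consequences within the set.

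- **ORR.** These participants were treated and have no documented response, yet they leave the denominator instead of counting as non-responders. The rate can only rise.
- **PFS.** The clock starts at first dose and death from any cause is an event. A participant who dies before re-evaluation is outside the set, so that death is never counted. The set and the endpoint definition, given in the same section, do not fit together. OS would be affected in the same way if it were analysed in this set.

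Planned sample size and study period says that the efficacy results are to inform a later, adequately powered trial. Planning values that are too favourable would carry over into that trial's sample size. The point concerns the RECIST and time-to-event endpoints, not the pathologic endpoint, which needs a resected specimen.

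**Working it through.** **Inputs from the article.** Part 1 has 6 participants and Part 2 up to 26: 6 + 26 = 32, which matches the stated maximum. No power calculation is given, so there is no other design figure to reproduce. The first re-imaging is at Day 43, and the first follow-up visit has a window of ±3 days.

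**Inputs assumed.** The article does not say how many dosed participants will miss re-evaluation (k), how many will respond (r), or how many will be progression-free at Day 127. I take k = 2 to 6, r = 9 and 24 progression-free. All 32 are taken as dosed.

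**1. Time before entry to the set.** 43 − 1 = 42 days; with the visit window, 40 − 1 = 39 to 46 − 1 = 45 days. This is 42/126, or one third, of the interval to the second follow-up visit.

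**2. ORR.** All dosed: r/32. Efficacy set: r/(32 − k).

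| k | All dosed | Efficacy set | Difference (points) |
|---|---|---|---|
| 2 | 9/32 = 28.1% | 9/30 = 30.0% | +1.9 |
| 4 | 28.1% | 9/28 = 32.1% | +4.0 |
| 6 | 28.1% | 9/26 = 34.6% | +6.5 |

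The result changes little with r. For the same range of k, 10 responders give +2.1 to +7.2 points and 5 responders give +1.0 to +3.6.

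**3. PFS at Day 127, upper bound.** Suppose every excluded participant had died or had documented progression before re-evaluation. All dosed: 24/32 = 75.0%. Efficacy set: 24/30 = 80.0% (k = 2), 24/28 = 85.7% (k = 4), 24/26 = 92.3% (k = 6). The differences are +5.0, +10.7 and +17.3 points.

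**4. PFS when only some of the excluded had an event.** Take k = 4, with d of them dying before re-evaluation and the other 4 − d lost without an event and censored at Day 1. Those censored add nothing to Kaplan-Meier after Day 1. With 24 of the remaining 28 progression-free and no other censoring, the all-dosed estimate is 24/(28 + d).

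| d | All dosed | Efficacy set | Difference (points) |
|---|---|---|---|
| 0 | 24/28 = 85.7% | 85.7% | 0 |
| 1 | 24/29 = 82.8% | 85.7% | +3.0 |
| 2 | 24/30 = 80.0% | 85.7% | +5.7 |
| 4 | 24/32 = 75.0% | 85.7% | +10.7 |

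The PFS inflation therefore follows the number of excluded participants who had an event, not the number excluded.

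**5. How likely is any exclusion?** If each of 32 dosed participants independently misses re-evaluation with probability p, the chance of at least one is 1 − (1 − p)^32: 48% for p = 2%, 81% for 5% and 97% for 10%. The expected numbers are 0.6, 1.6 and 3.2. These values of p are assumptions. The 5% in the Background is a treatment discontinuation rate in advanced disease, not a rate of missed scans.

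**The case against.** **The ITT analysis recovers these participants.** Every participant at issue was enrolled and dosed, so each belongs to the ITT set and has a PFS start date. This largely stands: an early death is lost only within the efficacy set, not from every possible analysis. However, the article does not say that ORR or PFS will be reported in the ITT set, and the more specific sentence assigns the efficacy analysis to the re-evaluated set. The two sentences still need to be reconciled.

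**The set makes the first 42 days event-free.** A reader might infer this, but the documents support it only for deaths. No scan is scheduled before Day 43, so scheduled imaging cannot show progression earlier in any set, including all dosed. That comes from the imaging schedule. Progression found on an unscheduled earlier scan might still count.

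**Toxicity withdrawals drop out.** This holds only for those who leave before re-evaluation. The adverse event section stops dosing, not follow-up; a participant who stops treatment and is still scanned stays in the set.

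**The link to PFS is inferred.** The PFS sentences do not name the efficacy set. They follow directly from it, so this is the natural reading, but it is not stated. Likewise, whether a scan off schedule counts as re-evaluation is open.

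**The analysis plan will settle it.** Non-responder scoring and censoring rules are commonly left to that plan, and their absence here is no fault. The membership rule itself, however, is stated in the article, and a plan that follows it would inherit the problem.

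**Little depends on it.** Efficacy is descriptive or exploratory and has no test or threshold. Entry requires Child-Pugh A, ECOG 0 or 1 and fitness for surgery, so early deaths may be few. With 10 responders among 32, the exact 95% interval is 16.1% to 50.0%, much wider than the shift in ORR. This stands and limits the weight of the point.

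**Conclusion.** The point holds in a limited form. As written, the efficacy set removes dosed participants who have no re-evaluation from the ORR denominator, and it cannot count a death before re-evaluation, contrary to the PFS definition in the same section. The ITT set would include these participants but is tied to no endpoint.

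On the assumed inputs, ORR is 1.9 to 6.5 points too high. PFS is too high only to the extent that excluded participants died, or had documented progression, before re-evaluation. A reader might take 5 to 17 points as the expected PFS bias. The documents do not support that: it is the upper bound in which every excluded participant had an event, and the article gives no rate of early death or missed scans. If none of them had an event, the Kaplan-Meier estimate is essentially unchanged.

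Severity is low to moderate. The primary safety endpoint is unaffected, and the decision to proceed rests on toxicity, for which the safety set already includes everyone dosed.

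**What to change.** - Make all participants with at least one dose the lead set for ORR, PFS and OS. This set already exists as the safety set.
- For ORR, count a participant without an evaluable pre-resection scan as a non-responder.
- For PFS, count every death after first dose as an event, and censor other losses at the last assessment (Day 1 if there was none).
- Report the re-evaluated set as a labelled sensitivity analysis.
- State how the ITT set relates to these, including enrolled participants who were never dosed and so have no PFS start date.

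The cost is wording only, in the protocol or in the analysis plan that is still to be finalised. No extra participants, visits or data are needed. ORR may read a few points lower.

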### Outcome measures and endpoints

Primary study endpoints include rate of patients experiencing a surgery delay to Day 89 or later and determination of safety and tolerability of the nivolumab/ipilimumab combination based on National Cancer Institute Common Terminology Criteria for Adverse Events (NCI CTCAE) v5.0 criteria from nivolumab and ipilimumab initiation to 126 days later.

Secondary endpoints include ORR on pre-resection imaging at day 42 according to the RECIST v1.1 criteria and pathologic response rate on evaluation of the resected specimen. Exploratory endpoints are PFS rate and OS at day 126 and every 4 months thereafter and identity of biomarkers of response to nivolumab and ipilimumab using high-throughput technologies.

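### Follow-up imaging instructions conflict and the PFS landmark sits mid-window; either can bias the exploratory PFS upward

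*Protocol article*

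**What the plan says.** **Imaging (Protocol article, Study procedures).** Screening comprises "baseline tumour imaging including computed tomography (CT) scan of the chest, abdomen and pelvis", together with a contrast-enhanced MRI of the liver. For the scans before surgery (Day 43), after surgery (Day 127) and later, the text reads "and 4-monthly thereafter, tumour imaging will be repeated using contrast enhanced MRI". The only CT named after that is a triple-phase CT of the liver, for intrahepatic staging when MRI is contraindicated. The same paragraph then adds: "The same method used for assessment at baseline must then be used at all subsequent time points". RECIST 1.1 is the stated basis for PFS.

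**Landmark.** Outcome measures and endpoints says "Exploratory endpoints are PFS rate and OS at day 126 and every 4 months thereafter". Statistical analysis says "Proportions of participants who do not progress and who are alive at Day 127 (FU2) and 4-monthly time-points thereafter will also be estimated", directly after planning Kaplan-Meier plots from start of treatment to the date of progression or death. In Study procedures, FU2 takes place 126 days (± 7 days) after first dose, and after that "participants will be assessed every 4 months (± 7 days) thereafter to collect information regarding disease status and survival".

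**The concern.** Two features of the PFS assessment can push the estimate in the favourable direction.

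First, the imaging sentence and the same-method sentence do not ask for the same scans. A site that follows the imaging sentence does not re-image the chest. Extrahepatic metastasis is an exclusion criterion, so any extrahepatic lesion seen later is new, and the article does not limit RECIST 1.1 progression to the liver. If sites differ in what they scan, PFS means different things within a cohort of at most 32. An analysis plan cannot recover scans that were never taken.

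Second, progression is mostly dated by the scan that finds it. A curve read at the middle of a visit window counts as progression-free those participants whose FU2 scan falls late in the window, even if they have already progressed.

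PFS supplies the trial's preliminary evidence of long-term disease control, and the efficacy data are meant to inform a later powered trial. With a single regimen there is no comparator in which such a bias would cancel.

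**Working it through.** **A. Imaging: the instructions side by side**

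| Time point | Imaging sentences | Same-method sentence, read literally |
|---|---|---|
| Baseline | Body CT (chest to pelvis) plus liver MRI | sets the method |
| Day 43, Day 127, 4-monthly | Contrast-enhanced MRI (liver CT if contraindicated) | Body CT plus liver MRI |

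The two columns agree at baseline and differ at every later scan. If the imaging sentence governs, the upward bias in a PFS rate is e × u. Here e is the share of participants whose only progression by that time is extrahepatic, and u is the share of those not found by other means. The documents give neither. For illustration only, with u = 1 and e assumed at 0, 2, 5 or 10%, the bias is 0, 2, 5 or 10 points; with u = 0.5 it is half that. These are not estimates for this trial.

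**B. Landmark: the arithmetic**

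1. The plan's own day reproduces: first dose on Day 1, plus 126 days, is Day 127. The ± 7-day visit window is Days 120 to 134, which is 15 days with Day 127 at its centre.
2. Days after the landmark but inside the window are 128 to 134, so 7 of 15 (46.7%). If day 126 were meant as study Day 126, it would be 8 of 15 (53.3%).
3. Bias of a strict Day 127 read = q × s, where q is the share whose progression is first found at the FU2 scan and s is the share of those scans dated after Day 127. With s = 46.7% and q assumed at 5, 10, 20 or 30%, the bias is 2.3, 4.7, 9.3 or 14.0 points. It is 0 if no scan is late and equals q if all are.
4. Constant-hazard illustration. Let S(t) = S(127)^(t/127), with scans at Day 43 and evenly over Days 120 to 134, and progression found only by scan. The value read at Day 127 is about 7/15 × S(43) + 8/15 × S(123.5), where 123.5 is the mean of Days 120 to 127. For a true 80%: S(43) = 0.927 and S(123.5) = 0.805, giving 0.433 + 0.429 = 0.862.
5. A simulation of 400,000 patients (scans at Day 43 ± 3, 127 ± 7 and 249 ± 7) gives:

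| True PFS at Day 127 | Read at Day 127 | Difference (points) | Read at Day 134 |
|---|---|---|---|
| 90% | 93.2% | 3.2 | 90.0% |
| 80% | 86.2% | 6.2 | 80.0% |
| 70% | 79.1% | 9.1 | 70.0% |
| 60% | 71.9% | 11.9 | 60.1% |

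6. A rough anchor: the Background says most patients recur within 2 years of surgery and that recurrence can reach 70%, with no time attached to the 70%. Assuming 50 to 70% progression by 2 years from first dose and the same constant hazard, a strict Day 127 read is 3.6 to 5.9 points too high. That is 32 × 0.036 = 1.2 to 32 × 0.059 = 1.9 participants.
7. For scale, the 95% half-width 1.96 × √(p(1−p)/32) is 10.4, 13.9 and 15.9 points at p = 90, 80 and 70%.

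**The case against.** A reader might infer that follow-up drops the body CT, that extrahepatic progression goes unseen, and that PFS is therefore overstated. The documents do not support that. The same-method sentence, taken literally, keeps the CT. The schedule of assessments is in Supplementary Table 1, which is not shown and may settle the matter. Deaths count as PFS events whatever the imaging, and disease status is collected every 4 months. No progression rate or extrahepatic share is given for this population. What stands is that the paragraph gives conflicting instructions. One could read the same-method sentence as covering only the choice between MRI and CT for the liver. That removes the contradiction, but it leaves the chest without any named follow-up scan, so the clarification is still needed.

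On timing, the landmark is labelled FU2 and the proportions are listed separately from the Kaplan-Meier plots, so status at the visit is a natural reading; on that reading there is no timing bias. The ± 7 days is attached to visits, while imaging is set for Day 127 without a window, so carrying the window over to scans is an inference. The landmark convention can also be left to the analysis plan. Day 126 and Day 127 may be one day counted two ways (days elapsed against study day). The constant hazard is doubtful, because liver resection falls between the Day 43 and Day 127 scans. All of this is fair. It makes the timing point conditional but does not remove it, since the text never says how the proportion is to be obtained.

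Finally, over true PFS of 90 to 70% the illustrated shifts are smaller than the sampling half-width. That limits the severity, although a systematic upward shift does not average out as sampling error does.

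**Conclusion.** The imaging instructions in Study procedures contradict each other as worded and need reconciling. If the MRI sentence is followed, extrahepatic progression may be missed and the exploratory PFS can be overstated; the direction is clear, but the size cannot be computed from the documents.

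The timing point holds conditionally. If the landmark is read strictly off the curve and scans follow the visit window, the overstatement is about 3 to 12 points for true PFS of 90 to 60%, assuming a constant hazard, evenly spread scans and progression found only by scheduled scan. If the proportion is taken by FU2 status, it is zero.

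Severity is minor. PFS is exploratory and descriptive, the decision to go on to a phase II trial rests on toxicity, and the primary safety conclusion is unaffected.

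**What to change.** 1. Reconcile the follow-up imaging sentence with the same-method rule by stating whether the baseline CT regions are re-imaged after baseline. If they are not, label the endpoint intrahepatic PFS (intrahepatic progression or death) and report extrahepatic findings separately.
2. Use one day count for the landmark, so that day 126 and Day 127 agree across the endpoint and analysis sections.
3. State that the proportions are classified by disease status at the visit. Alternatively, read the curve at the end of each visit window: Day 134, then each 4-monthly point plus 7 days.

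Items 2 and 3 cost only wording. Item 1 costs wording too: it either confirms scans that the same-method rule already calls for or narrows the endpoint label. It is best settled while follow-up scans are still to be taken, because it cannot be repaired at analysis.
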